#### Interim analyses {21b}

No interim analyses are planned.

#### Methods for additional analyses (e.g., subgroup analyses) {20b}

Subgroup analyses will be done based on age at transplantation (≤ 40 years vs. > 40 years), sex, pretransplantation degree of CoNV (0–1 quadrant vs. more than 1 quadrant), number of previous grafts (0 vs ≥ 1), presence of systemic immunosuppression (yes vs. no). The expected gender distribution is 50–50, as no known gender-related factors affect CoNV, efficacy, or safety of the CXL procedure, or transplantation-associated parameters.

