#### Eligibility criteria {10}

Eligibility for patients: Male and female patients aged ≥ 18 years with pre-vascularized corneas ≥ 2 corneal quadrants with the need for corneal transplantation due to central corneal opacification and low visual acuity due to this condition can be included in the study.

Patients who qualify for the study and want to participate must sign a written informed consent (IC) before inclusion. Exclusion criteria include certain eye conditions (dysregulated glaucoma, active uveitis, or corneal ulcer), allergies, contraindications to medication or surgery, significant medical conditions, and inability to comply with the study protocol.

Eligibility for study centers and surgeons: All study centers must have at least one expert corneal surgeon. To ensure follow-ups and if repetition of CXL is needed, another ophthalmologist will be involved.

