### Intervention description {11a}

pKPL replaces all layers of the diseased central cornea with an allogeneic healthy graft from a deceased donor. pKPL will be performed as a standard full-thickness penetrating procedure, and the graft (individualized size between 6.5 and 8.25 mm in diameter) will be secured with at least 16 interrupted (or double running star-shaped) 10-0 nylon sutures.

CXL is a corneal treatment involving riboflavin and irradiating the cornea with UV-A light. An accelerated protocol is used, which involves higher illumination intensity (9 mW/cm^2^) and shorter UV-A irradiation time (10 min) [18]. A shield protects the limbus during the procedure to prevent damage to the limbal stem cells as we plan to irradiate the complete cornea. CXL will be performed in the intervention group to stabilize the recipient cornea and to reduce CoNV 8 to 10 weeks before pKPL. The control group will undergo pKPL without prior CXL. CXL can be repeated once at least 14 days before transplantation if CoNV is not completely regressed.

In case of residual CoNV on the day of transplantation, fine needle diathermy will be used in the intervention group. It involves coagulating blood vessels using a monopolar cautery unit and a bent needle. In the control group, no fine needle diathermy will be performed.

Postoperatively, all patients will be treated with topical corticosteroids and antibiotics, and a systemic carboanhydrase inhibitor will be given to reduce intraocular pressure on the transplant.

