### Relevant concomitant care permitted or prohibited during the trial {11 d}

There are no restrictions on local and systemic therapies for patients receiving keratoplasty, including immunosuppressants. Topical steroids will be used postoperatively, with monthly reduction, topical antibiotics for two weeks, and cycloplegia during the first week. Systemic carboanhydrase inhibitors will reduce pressure on the transplant, and topical steroids and antibiotics are used and tapered as needed. Patients with corneal pathology due to herpesvirus will be treated according to guidelines using broad antivirals.

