Sufficient regression of CoNV after 1st CXL and only after 2nd CXL	Regression of CoNV > 50% (intervention arm only)	Value (yes/no)	Proportion	After 1st CXL and after 2nd CXL
Recurrence of CoNV	Recurrence (after sufficient regression was reached; intervention arm only)	Value (yes/no)	Proportion	After CXL (until transplantation) and after transplantation (within 24 months)
Visual acuity (BCVA)	ETDRS charts (transformed to logMAR)	Value	Mean	Prior to CXL, prior to transplantation, and 3, 6, 12, 18, and 24 months after transplantation
Vision-related quality of life	Overall score of NEI-VFQ25	Value	Mean	Prior to CXL, prior to transplantation, and 3, 6, 12, 18, and 24 months after transplantation
Infections	Active infectious keratitis or corneal ulceration	Value (yes/no)	Proportion	Within 24 months
Delayed wound healing	Delayed wound healing: corneal epithelium not closed (delay) or closed (no delay)	Value (yes/no)	Proportion	Within 24 months after transplantation
Graft dehiscence	Graft dehiscence characterized by leakage of aqueous humor	Value (yes/no)	Proportion	Within 24 months after transplantation

Survival analysis techniques will analyze primary and key secondary endpoints, allowing all patients to contribute information for however long they were followed up. The calculation of the scales of the NEI-VFQ follows the respective manual; missing values will be handled as described therein [19, 20].

The safety analysis includes calculating and comparing specified complication rates (see secondary endpoints), adverse events, and device deficiencies. Furthermore, descriptive methods are used to assess the homogeneity of the treatment groups. Analyses will be done using SAS (SAS Institute Inc., Cary, NC, USA) or IBM SPSS Statistics (IBM, Armonk, NY, USA).

Subgroup analyses will be done based on age at transplantation, sex, pretransplantation degree of CoNV, number of previous grafts, and presence of systemic immunosuppression.

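### The 0–1 versus more than 1 quadrant subgroup cannot be used: eligibility requires at least 2 quadrants, so the 0–1 stratum is either empty or practically without controls

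*Protocol article*

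**What the plan says.** In the protocol article, Methods for additional analyses {20b} lists five subgroup factors with their cut-points. One is "pretransplantation degree of CoNV (0–1 quadrant vs. more than 1 quadrant". Statistical methods {20a} names the same factor without a cut-point: "pretransplantation degree of CoNV, number of previous grafts, and presence of systemic immunosuppression". Neither section gives the visit at which the degree of corneal neovascularization (CoNV) is read for this purpose.

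Eligibility criteria {10} requires "pre-vascularized corneas ≥ 2 corneal quadrants with the need for corneal transplantation". Intervention description {11a} gives CXL to the intervention arm only, with the stated aim "to reduce CoNV 8 to 10 weeks before pKPL". For the other arm it says "The control group will undergo pKPL without prior CXL" and "In the control group, no fine needle diathermy will be performed".

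The primary log-rank test in {20a} is stratified by the number of affected quadrants, and there the text ties the count explicitly to baseline.

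**The concern.** The lower category lies wholly below the entry threshold. An eye can get there only by losing vessels after enrolment, and the trial offers a vessel-reducing procedure to one arm only. The subgroup variable is therefore either constant at entry or partly a result of the treatment being tested.

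Background and rationale {6a} says that rejection depends on how heavily the recipient bed is vascularised. The natural purpose of this subgroup is thus to see whether CXL works differently at different vessel burdens. The Discussion foresees a confirmatory trial if this one succeeds. A table showing good results in 0–1 quadrant eyes and poor results in the rest could be taken as guidance on whom to enrol next, when it may reflect only how the strata were formed.

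**Working it through.** **Inputs from the article.** The total is 110, allocated 5:4 (Trial design {8}, Sample size {14}). The split reproduces: 110 × 5/9 = 61.1 and 110 × 4/9 = 48.9, so 61 CXL and 49 control. The entry threshold is 2 quadrants in both arms ({10}). Vessel-reducing procedures in controls: none ({11a}). Control rejection at 2 years: 50% ({14}). The counts below treat every randomised patient as operated.

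**Assumed, not in the article.** The share r of CXL eyes that fall to 0–1 quadrant before transplantation is taken as 30–70%.

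**Stratum counts under each reading**

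| Value taken | 0–1 quadrant, CXL vs control | More than 1, CXL vs control |
|---|---|---|
| Before CXL | 0 vs 0 | 61 vs 49 |
| After CXL, r = 30% | 61 × 0.3 ≈ 18 vs 0 | 43 vs 49 |
| After CXL, r = 50% | about 30 vs 0 | about 30 vs 49 |
| After CXL, r = 70% | 61 × 0.7 ≈ 43 vs 0 | 18 vs 49 |

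The zeros for controls follow from the entry threshold and the treatment description and need no assumption about r. They hold for protocol-conforming controls without spontaneous regression.

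**Which reading is likelier.** Section {20a} says *at baseline* when it means the entry count, while {20b} says *pretransplantation*. The post-CXL reading is also the only one under which the 0–1 category has members. This is an inference, and the conclusion does not depend on it.

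**What the upper stratum compares under the post-CXL reading.** Its CXL eyes are those whose vessels did not fall to 0–1 quadrant, whereas its controls are essentially the whole control arm. Randomisation does not protect that contrast.

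**Illustration of possible bias.** Suppose CXL has no effect and overall rejection is 50%. Let s be the share of CXL eyes staying above one quadrant, k their rejection hazard relative to the other CXL eyes, and x the 24-month rejection-free proportion in those other eyes. Then (1 − s)x + s·x^k = 0.5.

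- For s = 0.4 and k = 2: x = [−0.6 + √(0.36 + 0.8)] / 0.8 = 0.596. Rejection in the upper CXL stratum is 1 − 0.596² = 0.644, so 64% against 50% in controls.
- For s = 0.3–0.5 and k = 1.5–3, the figure runs from 57% to 77%.
- With r = 30–70% and a hazard in regressing eyes of 0.5–0.7 times that in the others, the upper stratum shows about 54–67% and the lower about 34–46%.
- With k = 1 both strata show 50% and there is no bias.

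Neither s nor k is in the article. These figures show that a spurious difference can arise, not how large it will be.

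**The case against.** The strongest reply is that this is one of five additional subgroups in a trial that calls itself exploratory, and that the primary test uses baseline quadrants. That stands, and it limits the consequence. It does not rescue the cut-point. The timing of a measurement may be left to an analysis plan, but here the article states a specific cut that conflicts with its own eligibility rule.

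Several stronger readings are tempting and are not supported:

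- *The article specifies a post-CXL measurement.* It says only that the value is pretransplantation and names no visit.
- *The lower stratum will contain no control at all.* The modified intention-to-treat set keeps patients who breach entry criteria (Analysis populations), spontaneous regression is conceivable, and {11 d} says "There are no restrictions on local and systemic therapies for patients receiving keratoplasty, including immunosuppressants". A stray control is possible, though too few for a comparison.
- *The upper stratum is the CXL non-responders.* The article defines sufficient regression as a loss of more than 50% of CoNV (Objectives {7}, Table 3), not as a quadrant count. An eye with four affected quadrants could meet that and still have more than one affected. The two-class illustration is therefore a simplification.
- *The upper stratum is biased against CXL by a known amount.* Size and direction depend on the assumed prognosis of eyes that stay above one quadrant.
- *The systemic immunosuppression subgroup has the same flaw.* Nothing in the article says that CXL changes immunosuppression, {20a} describes the related Cox covariate as treatment for other diseases, and its ascertainment date is a detail commonly left to the analysis plan. No finding is made on it.

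**Conclusion.** The cut-point is incompatible with the entry criterion, and the subgroup fails under both readings. Before CXL it makes no split: 0 versus 0 and 61 versus 49. After CXL it gives one stratum with practically no controls, where no treatment effect and hence no interaction can be estimated, and another in which the CXL eyes are selected on a post-randomisation effect of treatment.

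That conclusion rests on the entry threshold and on controls receiving no vessel-reducing procedure. Only the stratum sizes under the post-CXL reading need an assumption (r = 30–70%). The bias percentages rest on further assumptions and should not be cited as estimates.

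The primary analysis is unaffected. The point should be corrected before the analysis is fixed, but it does not threaten the trial's main result.

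**What to change.** In {20b}, replace this subgroup with the number of affected quadrants at baseline, before any CXL, and put the cut inside the eligible range. A split of 2 versus 3–4 is one example; the article fixes no grouping, so the choice is the sponsor's. State the measurement visit, because Table 2 places the first CXL at the baseline visit itself. Bring the wording in {20a} into line.

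Preferably assess the subgroup by a treatment-by-subgroup interaction in the Cox model, reported as exploratory with confidence intervals. If either category held 30–70% of eyes (an assumption), each stratum would have about 18–43 CXL eyes and 15–34 controls (49 × 0.3 to 49 × 0.7), so both would contain a randomised contrast.

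Report vessel burden after CXL and before transplantation descriptively only.

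The cost is one sentence in {20b} and in the analysis plan. The baseline quadrant count is already needed for the stratified log-rank test, so no new data are required.

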#### Methods in analysis to handle protocol non-adherence and any statistical methods to handle missing data {20c}

In general, missing data will not be imputed. Unless indicated otherwise, summary statistics will be reported for observed data only. The number of missing values will be given. Survival analysis techniques will analyze primary and key secondary endpoints, allowing all patients to contribute information for however long they were followed up. In calculating the scales of the NEI-VFQ, missing values will be handled as described in the manual [19, 20].

### Analysis populations

The primary analysis set is the modified intention-to-treat analysis population, which includes all randomized patients who gave IC regardless of conformance to further inclusion/exclusion criteria, performed baseline assessment, and received surgery. Patients in the assigned treatment group will be analyzed irrespective of successful CXL.

A per-protocol (PP) population will be analyzed, excluding patients who do not fulfill major inclusion criteria or have other major protocol violations. Before the final analysis, the lead investigator (or representative) will blindly review all protocol violations.

The safety population includes all randomized patients with baseline assessments (this includes patients who did not receive surgery). The analysis is according to the treatment received.

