### Criteria for discontinuing or modifying allocated interventions {11b}

Drop-out or early discontinuation indicates a patient who has signed an IC, was eligible and enrolled with at least one trial-specific assessment, and discontinued the clinical trial for any reason before the end of the trial, as defined in the trial protocol. Reasons for drop-out/discontinuation are defined as withdrawal upon participant´s request; investigator-initiated discontinuation (e.g., medical reasons); lost to follow-up: cessation of participation without notice or action by the patient; sponsor-initiated discontinuation. Reasons for sponsor-initiated discontinuation may be insufficient regression of CoNV or prolonged healing phase after CXL so that the timeframe to the pKPL can not be respected.

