### Sample size {14}

Sample size calculation is based on the primary endpoint, time from surgery to the first graft rejection episode, comparing the intervention and control groups using the log-rank test. The expected rejection rate in the control group was estimated using rates given in previously published studies [6, 21]. An overall 2-year rejection rate of 50% was assumed for the control group. The study was powered to detect a reduction in the 2-year rejection rate from 50 to 25% (hazard ratio 0.42) with 80% power at a significance level of 0.05 (assuming exponential survival curves and accrual of 22 months, with a subsequent follow-up period of at least 24 months). An allocation rate of 5:4 and continuous loss-to-follow-up cumulating to 20% at 2 years was accounted for, yielding a total sample size of 110 (intervention group: *n* = 61, control group: *n* = 49). Calculations were performed using SAS 9.4 (Proc Power).

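### Graft dehiscence and delayed wound healing are compared as simple proportions, and the only safety set includes patients who never received a graft

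*Protocol article*

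**What the plan says.** Three parts of the protocol article bear on this.

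- **Endpoint and summary measure** (Statistical methods {20a}, Table 3). The dehiscence endpoint is "Graft dehiscence characterized by leakage of aqueous humor". It and delayed wound healing are scored yes/no, aggregated as a proportion, with a window that starts at transplantation and lasts 24 months. Infections are also a proportion over 24 months, but that window is not tied to transplantation. The same table derives graft survival and rejection-related graft failure from a survival curve.
- **Where they are analysed** ({20a}, text after Table 3). "The safety analysis includes calculating and comparing specified complication rates", with a pointer back to the secondary endpoints, alongside adverse events and device deficiencies.
- **Who is counted** (Analysis populations). The safety set is every randomised patient with a baseline assessment, and "this includes patients who did not receive surgery". Patients are grouped by treatment received. The modified intention-to-treat set, by contrast, requires surgery.

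Three further places set the context. Section {11b} allows the sponsor to discontinue a patient for "insufficient regression of CoNV or prolonged healing phase after CXL" when the transplantation window can then not be kept. Section {20c} rules out imputation in general, bases summaries on observed data and promises the number of missing values. Section {14} plans for "continuous loss-to-follow-up cumulating to 20% at 2 years", while section {18b} expects loss to be low.

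**The concern.** Both complications require a graft, yet they are assigned to an analysis whose only defined set includes people without one. Taken literally, those people enlarge the denominator and can never contribute an event. The discontinuation reasons quoted from {11b} can arise only after CXL, so the extra denominator could collect in the experimental arm and make its graft complications look rarer than they are.

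A second, smaller issue is that a simple proportion has no rule for patients whose follow-up ends before 24 months, so the result depends on how they are scored. Safety is a stated secondary aim, and section {11c} gives the discovery of rare complications as one reason for the 5:4 allocation. The comparison should therefore not depend on an unstated scoring choice.

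**Working it through.** **Inputs from the article.** Arm sizes are 61 (CXL) and 49 (control). Planned loss is 20% at 2 years. The article gives no complication risk and no expected number of patients without surgery, so those are assumptions here, shown as ranges.

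**The plan's own figures.** The split follows from 110 × 5/9 = 61.1 and 110 × 4/9 = 48.9. The total of 110 can be reproduced (two-sided 0.05 assumed, since sidedness is not stated):
- HR = ln 0.75 / ln 0.50 = 0.415.
- Events = (1.960 + 0.842)² / [(5/9)(4/9)(ln 0.415)²] = 41.1.
- Average event probability without loss, for 22 months' accrual plus 24 months, is 0.469, so N = 87.6. Then 87.6/0.8 = 109.5, or 110.

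This shows where the 20% comes from: it is a planning allowance for the primary endpoint. No figure for complications exists to reproduce.

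**Step 1: patients without a graft.** Suppose they are scored event-free. Then displayed risk = p × (n − m)/n, with p the true risk among transplanted patients, n the arm size and m the number not transplanted. With p = 10% in both arms:

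| Not transplanted (CXL, control) | CXL shows | Control shows | Apparent ratio |
|---|---|---|---|
| 3/61, 0/49 | 10% × 58/61 = 9.5% | 10.0% | 0.95 |
| 6/61, 0/49 | 10% × 55/61 = 9.0% | 10.0% | 0.90 |
| 12/61, 0/49 | 10% × 49/61 = 8.0% | 10.0% | 0.80 |
| 6/61, 5/49 | 9.0% | 10% × 44/49 = 9.0% | 1.00 |

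The ratio in each row does not depend on p. Conversely, a true CXL risk of 10% × 61/(61 − m) = 10.5%, 11.1% or 12.4% (m = 3, 6, 12) would be displayed as 10%. If patients without a graft are instead treated as unobserved, as {20c} permits, m leaves the denominator and the dilution is zero.

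**Step 2: loss to follow-up.** Assume constant hazards for the event, λ = −ln(1 − p)/24, and for loss, γ = −ln(0.8)/24. The probability that an event is seen before loss is [λ/(λ + γ)] × [1 − exp(−24(λ + γ))].
- For p = 10%: 0.1054/(0.1054 + 0.2231) = 0.3207; 1 − 0.9 × 0.8 = 0.28; product 0.0898.
- Lost patients scored event-free: 9.0%.
- Observed only, read as events/(events + event-free completers): 0.0898/(0.0898 + 0.72) = 11.1%.
- For p = 20% the same two scorings give 18.0% and 22.0%.

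**Step 3: early events.** If the 10% risk falls entirely in the first 3 months, then λ = −ln(0.9)/3 and the formula is applied over 3 months. Scoring lost patients event-free gives 9.9%, almost no bias. Counting only events and completers gives 0.0986/(0.0986 + 0.72) = 12.0%.

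**The case against.** The strongest reply is that the article never says a patient without a graft, or one lost to follow-up, counts as event-free. The endpoint window starts at transplantation, so a patient never transplanted has no window and arguably no observed value. Under {20c} that patient would then drop out, and the dilution with them. An article may also leave the denominator of each safety table to the full protocol or analysis plan. Missed surgery has other stated causes open to both arms (participant request, medical reasons, loss to follow-up), and {11b} says only that the CXL-related reasons may apply. The 20% is a planning figure, and {18b} expects little loss.

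Most of this stands. It rules out the stronger reading that a reader might infer, namely that complication rates will be too low in both arms and that CXL is thereby favoured. No sentence fixes the scoring that this needs. Under the observed-data rule, loss pushes the rate up rather than down, and equal loss favours neither arm. Nor is the safety set itself wrong. It suits adverse events and device deficiencies, and also infections, which may occur between CXL and surgery.

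One part of the reply does not stand. The article has not left the matter wholly open: it chose the proportion as summary measure, placed these two outcomes in the safety analysis and named one safety set that expressly contains patients without surgery.

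**Conclusion.** A minor point that holds in limited form. As written, the plan compares two complications that need a graft, as simple proportions, without a denominator restricted to patients who have one.

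- **Missed surgery.** The possible distortion is an apparent risk ratio of 0.95 to 0.80 when true risks are equal. This rests on three assumptions: 3 to 12 of 61 CXL patients go without a graft, none do in control, and those patients are scored event-free. It is zero if they are treated as unobserved, and the ratio returns to 1.00 if missed surgery is balanced.
- **Loss to follow-up.** At the planned 20% and constant hazard, a 10% risk shows as 9.0% or 11.1%. The direction depends on scoring and is not fixed by the article. For early events the bias is close to nil when lost patients are scored event-free.

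Only missed surgery, not equal loss, could act mainly on the CXL arm. Infections are outside the point, because their window does not start at transplantation.

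**What to change.** State in the protocol or analysis plan that:

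1. graft dehiscence and delayed wound healing are computed among transplanted patients, grouped by treatment received, as 24-month cumulative incidence from surgery with confidence intervals;
2. the number of patients not transplanted is reported by arm with reasons;
3. infections and other events between CXL and surgery are reported separately;
4. the full safety set is kept for adverse events, serious adverse events, device deficiencies and infections.

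The cost is a few sentences and standard code. Table 3 already uses survival-curve rates for the graft endpoints, and section {22} already records when each adverse event begins and ends, so no new data are needed provided these complications are recorded as adverse events. The downside is slightly more analysis work and a somewhat smaller denominator for these two outcomes.
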